### Interventions

Participants in Group A will receive a course of ethinyl estradiol (0.03 mg) + Levonorgestrel (0.15 mg) combined oral contraceptive pills over three menstrual cycles. In Group B, participants will be administered dydrogesterone, with 10 mg taken twice daily for ten days during the luteal phase. This protocol will be repeated across three consecutive menstrual cycles.

Criteria for discontinuing or modifying allocated interventions will be clearly defined in our study. These criteria may include, but are not limited to, the development of severe adverse events, non-compliance with the treatment protocols, or the emergence of conditions that contraindicate further participation. In such cases, the participant will be withdrawn from the study, and the reasons for discontinuation or modification will be documented.

To ensure participant adherence to allocated interventions, we will implement the following strategies:
•Regular follow-up appointments and reminders to participants regarding treatment regimens.•Monitoring of participant compliance through self-reporting and pill counts for both intervention groups.•Tracking participant satisfaction and addressing any concerns or issues that may affect adherence.•Continuous communication between the research team and participants to address any questions or issues related to the interventions.

Participants will be advised to avoid the use of other hormonal medications or treatments during the study period, as these may confound the results. However, the use of non-hormonal over-the-counter medications will be allowed as needed, and these instances will be recorded.

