### Primary outcome measures

**Effectiveness assessment:**
1.
**Regression of cysts:** To monitor the regression of ovarian cysts, we will conduct regular ultrasound evaluations. Participants from both study groups will undergo ultrasound assessments after each menstrual cycle. These assessments will continue until either the cysts dissipate or for a maximum duration of three months.2.
**Menstrual pattern changes:** To observe shifts in menstrual patterns, we will have participants maintain menstrual diaries. Participants will record information regarding the frequency, regularity, duration, and volume of their menstrual cycles. Data will be collected at each follow-up appointment, allowing us to track any changes over time.

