### Follow-up

An ultrasound evaluation will be integrated into the study’s follow-up process. Participants enrolled in both study groups will undergo thorough ultrasound assessments after each menstrual cycle. This evaluation will continue until either the cysts dissipate or for a maximum duration of three months.

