### Statistical analysis

The statistical analysis plan for this study will involve several key steps. Descriptive statistics will be used to summarize baseline characteristics of participants in both treatment groups. Continuous variables will be presented as means with standard deviations or medians with interquartile ranges, while categorical variables will be summarized as frequencies and percentages.

For the primary outcomes, the effectiveness and safety of the two treatments will be assessed separately. The regression of cysts within the three-month timeframe will be compared between groups using appropriate statistical tests, such as the Chi-square test or Fisher’s exact test. Changes in the menstrual pattern will be analyzed using paired t-tests or non-parametric tests if assumptions are not met.

Safety outcomes, including the duration of treatment needed and the incidence of side effects, will be compared using appropriate statistical tests, depending on the distribution of data. The impact on liver function tests and the occurrence of serious complications will be analyzed using appropriate statistical methods, potentially logistic regression, or survival analysis for time-to-event outcomes.

A comparative analysis between the two treatment groups will be performed using appropriate statistical tests, such as t-tests, Mann-Whitney U tests, or chi-square tests, depending on the nature of the data. Adjustments for potential confounders, such as age, BMI, and baseline cyst characteristics, will be considered using regression models. The significance level for hypothesis testing will be set at 0.05, and all tests will be two-tailed. Confidence intervals will be calculated where relevant.

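### Menstrual diaries are collected repeatedly, but the analysis names a paired t-test within an arm and fixes no cycle, per-woman summary or repeated-measures model

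*Protocol article*

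**What the plan says.** In the Protocol article, menstrual pattern change stands second under Primary outcome measures, in the effectiveness assessment. The source is a diary: "To observe shifts in menstrual patterns, we will have participants maintain menstrual diaries". It has four components: "Participants will record information regarding the frequency, regularity, duration, and volume of their menstrual cycles". Collection is repeated: "Data will be collected at each follow-up appointment, allowing us to track any changes over time".

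The number of cycles must be inferred. The Interventions section says of treatment: "This protocol will be repeated across three consecutive menstrual cycles". The Follow-up section that describes ultrasound, which is done after each cycle, adds: "This evaluation will continue until either the cysts dissipate or for a maximum duration of three months". How long the diary runs, and whether a pre-treatment cycle is recorded, is not stated.

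The Statistical analysis section gives this outcome one sentence of its own: "Changes in the menstrual pattern will be analyzed using paired t-tests or non-parametric tests if assumptions are not met". A later paragraph provides for a general comparison of the two groups by tests "such as t-tests, Mann-Whitney U tests, or chi-square tests, depending on the nature of the data". Regression models are to be considered there too, but only to adjust for age, BMI, baseline cyst characteristics and similar confounders. Tests are two-tailed at 0.05.

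**The concern.** The data described and the test named do not fit each other, in two ways.

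- **Repetition.** The outcome is followed over time, with several correlated cycles per woman. A paired t-test takes one pair per woman, and an ordinary t-test, Mann-Whitney U test or chi-square test takes one value per woman. To apply any of them, someone must first choose a cycle or reduce the cycles to a summary. The text does neither, so the choice could be made after the data are seen.
- **Direction of comparison.** A paired t-test asks whether an arm changed from its own starting point. The trial's third objective is to compare the arms. Change that is significant in one arm and not in the other does not show that the arms differ.

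At stake are the precision of a primary outcome and the number of tests from which a result could be picked.

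**Working it through.** The documents give no figure on this point to reproduce, so the check sets out what each way of applying the named tests would mean.

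**Inputs from the Protocol article:** 42 women per arm before the dropout allowance (Sample size; used only as the analysable number, and whether it follows from its own formula is a separate matter); two-sided α = 0.05 (Statistical analysis); three cycles (inferred from Interventions and Follow-up).

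**Assumptions not in the documents:** within-woman correlation ρ between cycles of 0.3, 0.5 or 0.7, equal for all pairs; equal variance at each cycle; an illustrative arm difference of 0.5 SD of a single cycle.

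**1. One cycle kept, compared with all three.** The variance of a woman's three-cycle mean relative to one cycle is (1 + 2ρ)/3:

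- ρ = 0.3: 1.6/3 = 0.533
- ρ = 0.5: 2.0/3 = 0.667
- ρ = 0.7: 2.4/3 = 0.800

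Power by the normal approximation is Φ(0.5 × √(42/2) / √V − 1.96), where V is that ratio (V = 1 for a single cycle) and 0.5 × √21 = 2.291:

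- One cycle: Φ(2.291 − 1.96) = Φ(0.331) = 0.63
- ρ = 0.3: Φ(3.137 − 1.96) = Φ(1.177) = 0.88
- ρ = 0.5: Φ(2.806 − 1.96) = Φ(0.846) = 0.80
- ρ = 0.7: Φ(2.562 − 1.96) = Φ(0.602) = 0.73

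Exact t-based values are about one percentage point lower.

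**2. Each of three cycles tested separately at 0.05.** If the cycles were independent, the chance of at least one false positive for a feature would be 1 − 0.95³ = 0.143. Simulation with correlated cycles gives 13.9% at ρ = 0.2, 12.5% at ρ = 0.5 and 10.9% at ρ = 0.7, so about 11–14%.

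**3. One summary per woman.** An ordinary t-test on each woman's three-cycle mean, 42 per arm, had a simulated error rate of 5.0%, 5.1% and 4.9% at ρ = 0.2, 0.5 and 0.7. This route is valid and, with complete data, brings the whole power gain in step 1.

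**4. Cycles pooled as if each were a separate woman, for scale only.** In a between-arm test the design effect is 1 + 2ρ = 1.6, 2.0 or 2.4. The true two-sided error rate is 2 × P(Z > 1.96/√(1 + 2ρ)) = 12.1%, 16.6% or 20.6%. The protocol does not propose this.

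**The case against.** The strongest reply is that the named tests can serve. Averaging each woman's cycles and applying a t-test or Mann-Whitney test holds the error rate and gives the power gain shown. That is correct. A reader might infer that the named tests leave only three bad choices: dropping cycles, testing them one by one, or counting them as independent women. The documents do not support that, because a per-woman summary is a fourth, valid choice.

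Three other stronger readings also fail:

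- *Cycles will be counted as independent women.* Nothing says so, and a paired test points the other way, to one difference per woman. The 12–21% error rates describe a risk and not a plan.
- *Only single-value tests are allowed.* The non-parametric test is not named and could be one for several repeated measures. The between-group list is open, since it is introduced by "using appropriate statistical tests, such as t-tests, Mann-Whitney U tests, or chi-square tests, depending on the nature of the data".
- *The arms are never compared on this outcome.* The general comparison paragraph can cover it, although the outcome's own sentence does not.

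It can also be said that a condensed article leaves the choice of cycle, summary and model to a statistical analysis plan that is not shown. That would answer silence. Here, however, the article commits a primary outcome to a particular method, and that method neither compares the arms nor uses the repeated collection. A later plan that followed the sentence would inherit the mismatch.

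Finally, preferring a mixed model to a per-woman mean is partly taste. That stands, and either is acceptable.

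**Conclusion.** The concern holds in a limited form. The stated analysis of menstrual change does not match the stated data collection. It names a within-arm test on one pair per woman for an outcome recorded repeatedly in a comparative trial, and it ties neither that test nor the between-group examples to a cycle, a summary or a repeated-measures model.

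The likely cost is lost precision if one cycle is used, or a false-positive chance of about 11–14% per feature if each cycle is tested. The size of either rests on three recorded cycles and on assumed correlations. The power figures also rest on the illustrative 0.5 SD difference. The point is worth correcting because a primary outcome is affected. It does not show that the planned analysis would be invalid, since a sound per-woman summary remains open under the present wording.

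**What to change.** Replace the paired t-test sentence with one between-arm analysis for each numeric diary feature, using all recorded cycles. Either form will do:

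- a linear mixed model with a random intercept per woman and terms for arm, cycle number and, where recorded, the baseline value; or
- each woman's mean over her recorded cycles, compared between arms with adjustment for baseline where recorded.

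In both cases report one arm difference per feature with its 95% CI. Reduce regularity and frequency, which span cycles, to one result per woman. If volume is not recorded on a numeric scale, use an ordinal analysis or a per-woman summary. The change need not extend to ALT and AST, because the article does not assign liver tests to the paired t-test.

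The cost is a change of wording, slightly more analysis work and, for the mixed model, assumptions to check. No new data are needed, and the Study status section says that the trial has not started.

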### Inclusion criteria

Participants within the reproductive age range of 18 to 44 years, possessing ovarian cysts between 3 to 10 centimeters with a single compartment and precise contents, and having a body mass index (BMI) within the range of 18.5 to 29.9 will be considered for inclusion.

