### Sample size

Formula using mean difference

$$n1=n2=2\frac{{\left(Z_{\alpha }+Z_{\beta }\right)}^{2}\sigma^{2}}{{\left(\delta \right)}^{2}}$$

$$Z_{\alpha }=1.96$$

α=Type I error at 5% at both sides two tailed

$$Z_{\beta }=1.28=\text{Power at 90\%}$$

Dydrogesterone vs combined oral contraceptive pills for functional ovarian cysts (δ) = 0.3

Considering 30% superiority = (0.3*30)/100 = 0.09

Standard deviation = 1

Minimum sample size N =

$n1=n2=2\frac{{\left(1.96+0.09\right)}^{2}{\left(\;1\right)}^{2}}{{\left(0.09\right)}^{2}}=42\;\text{per group}$

Considering 10% drop out = 4

Total sample size required = 42 + 4 = 46 per group. Reference study.
^
5
^

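### Adjustment of the cyst-regression comparison for baseline cyst size is left to discretion, with no rule for whether the adjusted or the unadjusted result counts

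*Protocol article*

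**What the plan says.** All places are in the protocol article.

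- **Statistical analysis, cyst regression.** Regression within three months is to be compared between groups by suitable tests, with chi-square and Fisher's exact given as examples. Both are unadjusted.
- **Statistical analysis, adjustment.** "Adjustments for potential confounders, such as age, BMI, and baseline cyst characteristics, will be considered using regression models". The covariates are again examples. Nothing says whether a regression model would replace, accompany or rank below the unadjusted test.
- **Statistical analysis, error level.** "The significance level for hypothesis testing will be set at 0.05, and all tests will be two-tailed".
- **Inclusion criteria.** Women qualify by "possessing ovarian cysts between 3 to 10 centimeters with a single compartment", so cyst size is known before randomisation.
- **Allocation (both sections).** Randomisation is 1:1 by sealed envelope. No stratification by cyst size is described.
- **Sample size.** 42 per group, raised to 46 for dropout.

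**The concern.** Two things are at stake.

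**Precision.** The outcome is whether a cyst disappears within three months, and eligible cysts span more than a threefold range of diameter. The protocol itself lists cyst characteristics among the variables that may matter. If size does predict resolution, an unadjusted comparison in a trial of this size discards information already in hand.

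**Which result counts.** Adjustment is addressed but made optional, and the stated reason is confounding. In a randomised comparison baseline factors do not confound systematically. The reasons to adjust are precision and chance imbalance, and both call for a decision before the data are seen. As worded, the analyst can look at an unadjusted and an adjusted p-value and has no rule for choosing between them.

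**Working it through.** **1. The plan's own sample size.** The section gives "Dydrogesterone vs combined oral contraceptive pills for functional ovarian cysts (δ) = 0.3", then "Considering 30% superiority = (0.3*30)/100 = 0.09", and "Standard deviation = 1", with Z values 1.96 and 1.28. Its formula is n = 2(Zα + Zβ)²σ²/δ².

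- δ = 0.09: 2 × 3.24² / 0.0081 = 2,592 per group (2,595 by the exact routine).
- δ = 0.3: 2 × 3.24² / 0.09 = 233.3, so 234 per group.
- The expression as printed, with 0.09 where Zβ belongs: 2 × 2.05² / 0.0081 = 1,038.

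None of these gives 42. I therefore use 42 per arm below only as the number the trial expects to evaluate, not as a justified size.

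**2. Power with and without adjustment.** The protocol gives no resolution rates and no relation of size to resolution, so these are assumptions: 42 per arm; diameter uniform on 3 to 10 cm; log-odds of resolution linear in diameter; overall resolution rates in the two arms held fixed at 60% and 85%, or at 50% and 80%. Each setting has 3,000 simulated trials. Pearson chi-square is compared with a likelihood-ratio test from logistic regression on treatment and diameter, both at two-sided 5%.

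| Odds ratio per cm | Lower-rate arm (60%): resolution at 3 cm and 10 cm | Power, 60% vs 85%: unadjusted / adjusted | Power, 50% vs 80%: unadjusted / adjusted |
|---|---|---|---|
| 1.0 | 60%, 60% | 75% / 75% | 85% / 85% |
| 1.25 | 77%, 41% | 75% / 77% | 84% / 85% |
| 1.5 | 87%, 28% | 74% / 79% | 84% / 88% |
| 2.0 | 95%, 14% | 75% / 86% | 84% / 94% |
| 2.5 | 98%, 8% | 74% / 91% | 84% / 96% |

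From the unrounded powers, the gain is about 0 points with no relation, about 2 to 5 at odds ratios of 1.25 to 1.5 per cm, and about 9 to 16 at 2.0 to 2.5 per cm. The simulation error on a power near 75% is √(0.75 × 0.25 / 3,000) = 0.8 points. With no treatment effect, the rejection rate was 5.5 to 6.4% for chi-square and 4.7 to 6.0% for the adjusted test, so the gain is not bought with a looser test.

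**3. Choosing after seeing both.** A second simulation used log-odds 0.4 at 6.5 cm, a slope per cm, and a treatment odds ratio of 1 or 4.

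- Odds ratio 1: counting the trial positive if either test gives p < 0.05 led to a false-positive rate of about 6% when size has no effect, rising to about 9% at a slope of 0.7 per cm.
- Odds ratio 4: the two tests disagreed on significance in about 7%, 13% and 19% of trials at slopes of 0.3, 0.5 and 0.7.

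**4. Chance imbalance.** The SD of a uniform variable on 3 to 10 is 7/√12 = 2.02 cm. The SD of the difference in arm means is 2.02 × √(2/42) = 0.44 cm. A difference above 0.5 cm is 0.5/0.44 = 1.13 SDs, which occurs in about 25% of randomisations.

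**The case against.** **An unadjusted test is valid, and details belong to a statistical analysis plan.** The first part stands: chi-square or Fisher's exact is a legitimate primary analysis of a 1:1 randomised binary outcome, and chance imbalance does not invalidate it. The coding of covariates can also wait for a plan that is not shown. But the protocol is not silent here. It takes up adjustment and makes it discretionary, and that is what the point rests on.

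**A reader might infer that the primary test is fixed as an unadjusted chi-square and that power is certainly lost.** The text supports neither. The tests are given as examples, and no passage relates size to resolution. If there is no relation, nothing is lost.

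**Larger losses can be produced.** With the treatment odds ratio held at 4 within each cyst size, power was 78% vs 78%, 74% vs 77%, 65% vs 74% and 56% vs 69% (unadjusted vs adjusted) at slopes of 0, 0.3, 0.5 and 0.7 per cm. Part of that widening comes from the set-up: the overall risk difference shrinks from about 25 points at a slope of 0.3 to about 21 at 0.7. These slopes also imply odds ratios of about 8, 33 and 134 across the 7 cm range (e^2.1, e^3.5, e^4.9). The table above, with overall rates fixed, is the fairer guide. With a Wald test in place of the likelihood-ratio test, adjusted power was 75% at slopes 0.2 and 0.3, against 76% and 73% unadjusted, so weak relations bring little or nothing.

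**Nor is a marked size imbalance likely.** A gap above 0.5 cm arises in about one randomisation in four, and 0.5 cm is only about a quarter of the assumed SD.

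**Other remedies are defensible,** such as a stratified Mantel-Haenszel analysis, or an unadjusted primary with a named adjusted sensitivity analysis. Either would settle which result counts; the second would forgo the precision.

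**Conclusion.** The point holds in a limited form. The protocol leaves open whether the adjusted or the unadjusted comparison of cyst regression counts, and leaves to discretion an adjustment that costs no data and, in simulation, essentially no power. The benefit ranges from nil to about 16 points and cannot be narrowed from the protocol. The upper end needs resolution to fall from 95% or more at 3 cm to 14% or less at 10 cm in the 60% arm. The open choice of test carries a false-positive rate of about 6 to 9%.

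These figures assume 42 evaluable women per arm, uniform diameters, a log-linear size effect, a yes/no outcome at three months and the resolution rates shown. The point is secondary to the sample-size error: adjustment cannot bridge the distance from 42 to 234 or 2,595 per group.

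**What to change.** Replace the discretionary sentence, for cyst regression, with wording such as: *The primary comparison of cyst regression within three months is a logistic regression on treatment group with baseline maximum cyst diameter (continuous) as covariate, tested by likelihood ratio and reported as a standardised risk difference with 95% confidence interval. The chi-square or Fisher's exact test is supportive. Covariates will not be selected after seeing the data.* If age and BMI are also wanted, name them now. Describe the purpose as precision, not control of confounding.

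The cost is one or two sentences. Diameter is already needed for eligibility, treatment is unaffected, and the Study status section says the trial has not started, so the change can be made before any outcome is seen. The sample-size calculation needs its own correction.

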## Discussion

The present study protocol outlines a comprehensive framework for investigating the efficacy and safety of combined oral contraceptive pills (COC) and dydrogesterone in managing functional ovarian cysts. The study’s design and methodology reflect a systematic approach to addressing the clinical challenges posed by these cysts while contributing to evidence-based treatment decisions.

**Functional ovarian cysts and clinical significance:** Functional ovarian cysts are common among reproductive-aged women, often necessitating medical attention due to their potential to disrupt fertility and overall well-being. These cysts arise from the complex interplay of hormonal fluctuations and follicular development, with deviations from the norm occasionally resulting in cysts that require clinical intervention. The clinical significance lies in the potential for these cysts to cause discomfort, pain, and menstrual irregularities, thereby impacting the quality of life and reproductive potential of affected individuals.
^
6
^

**The rationale for study design:** The chosen study design, an interventional two-arm parallel comparative study, is apt for evaluating the relative efficacy and safety of COC and dydrogesterone. This design allows for direct comparison between the two treatments, enabling researchers to draw meaningful conclusions about their merits. By employing random allocation and well-defined inclusion and exclusion criteria, the study minimizes bias and enhances the validity of the results.
^
7
^

**Treatment options and therapeutic landscape:** The study’s focus on COC and dydrogesterone is well-founded, as both interventions have demonstrated potential in addressing functional ovarian cysts. With their hormonal regulation properties, COC may modulate the hormonal milieu to suppress cystic growth. Dydrogesterone’s specific luteal phase support properties offer an alternative mechanism of action, potentially influencing cyst resolution. This dual intervention approach enriches the understanding of treatment possibilities.
^
8
^
^,^
^
9
^

**Primary outcome measures:** The primary outcomes, centered around effectiveness and safety, encompass the regression of cysts, alterations in menstrual patterns, treatment duration, side effects, and complications. These outcomes holistically capture the impact of the interventions on both the physical and overall well-being of participants. Monitoring cyst regression and menstrual pattern changes offers insights into the interventions’ therapeutic effects, while evaluating safety profiles contributes to a comprehensive understanding of potential risks.

**Implications and future directions:** The findings of this study have far-reaching implications for clinical practice. The data generated from the study will aid clinicians in making informed treatment decisions, balancing effectiveness and safety considerations. Furthermore, this research sets the stage for more targeted investigations into the mechanisms of action of COC and dydrogesterone, potentially uncovering novel insights into the pathophysiology of functional ovarian cysts.

**Limitations and considerations:** It’s important to acknowledge potential limitations, such as the limited follow-up duration and the exclusive focus on two treatment options. Future studies could explore the effects of alternative interventions and longer-term outcomes, providing a more comprehensive understanding of functional ovarian cyst management.

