**Expected outcomes:**

The primary outcomes include evaluating the recession of cysts within three months, monitoring alterations in menstrual patterns (frequency, regularity, duration, and volume), assessing the necessary treatment duration, and observing potential side effects (e.g., nausea, vomiting, weight gain, and acne) and complications (e.g., thromboembolism, delayed menstrual cycles post-treatment, and interactions with other drugs). Data analysis will encompass descriptive statistics, comparative tests, and regression models to assess the primary outcomes. The significance level for hypothesis testing will be 0.05 with a two-tailed approach.

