## Introduction

Functional ovarian cysts, a prevalent occurrence among women of reproductive age, frequently require medical intervention due to their potential to disrupt fertility and overall health. These cysts originate from the intricate interplay of normal physiological processes involved in ovulation and follicular development.
^
1
^ However, in certain instances, deviations from this intricate balance can lead to the development of cysts that warrant medical attention. Such deviations can manifest as variations in size, persistence, or symptomatic expression, prompting clinical intervention to prevent complications and alleviate patient discomfort.

The management landscape for functional ovarian cysts comprises a spectrum of approaches, encompassing both surgical and medical modalities. Surgical interventions, while effective, often involve inherent risks and potential disruptions to reproductive function. On the other hand, medical options promise to preserve fertility and avoid invasive procedures. Despite the existing armamentarium, pursuing treatments that balance efficacy and safety remains an ongoing endeavor.
^
2
^
^,^
^
3
^

This study seeks to address this need by conducting a hospital-based interventional two-arm parallel comparative investigation to compare the effectiveness and safety of two distinct medical interventions – combined oral contraceptive pills (COC) and dydrogesterone. COC, renowned for their hormonal regulatory effects, have demonstrated potential in mitigating cystic growth. Conversely, dydrogesterone, a synthetic progestin, presents an alternative therapeutic avenue with its luteal phase support capabilities.
^
4
^

The primary objective is to evaluate the efficacy of these interventions in terms of cyst regression and their influence on the menstrual pattern. Additionally, the study will focus on assessing the safety profile, including potential side effects, treatment duration, and the occurrence of complications. The outcomes of this research will contribute essential insights to inform clinical decision-making, guide treatment strategies, and optimize patient care. By comparing the outcomes of these interventions in a controlled and systematic manner, this study advances our understanding of medical management approaches for functional ovarian cysts, ultimately enhancing the quality of care for women facing this common medical concern.

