### Allocation

The allocation sequence will be generated by a biostatistician, who is not directly involved in the enrolment process. The enrolment of participants will be conducted by clinical research coordinators, while the assignment of participants to interventions will be performed by a research pharmacist based on the allocation sequence. Due to the nature of the interventions, participants cannot be blinded. However, outcome assessors and data analysts will be blinded to the treatment assignments. Unblinding may be considered in the event of a medical emergency or if knowledge of the treatment assignment is deemed necessary for the safety and well-being of the participant. Unblinding will only occur when the unblinded status is required for clinical management.

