**Safety assessment:**
1.
**Duration of treatment:** We will determine the duration of treatment necessary for each participant by monitoring their response and progress during follow-up appointments. The treatment duration will be based on individual responses and the predefined treatment protocol.2.
**Monitoring side effects:** Participants will be encouraged to report any potential side effects during regular follow-up appointments and will also have access to a dedicated contact point for immediate reporting. Adverse events, including nausea, vomiting, weight gain, and acne, will be documented and assessed for severity and causality.3.
**Effects on liver function tests:** We will conduct regular blood tests to assess liver function. Liver function tests, including alanine aminotransferase (ALT) and aspartate aminotransferase (AST) levels, will be measured at specific intervals during the study. Any abnormal results will be monitored closely.4.
**Tracking critical complications:** We will monitor for critical complications such as thromboembolism, delayed menstrual cycles post-treatment, and potential interactions with other drugs through continuous review of participants’ medical records and regular assessments during follow-up appointments. In the event of a critical complication, immediate actions will be taken following our predefined clinical management plan.

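### Five or six outcome families are all labelled primary at two-sided 0.05 with no lead outcome, so the 5% error rate does not cover the trial's primary conclusion

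*Protocol article*

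**What the plan says.** The protocol article describes its primary outcomes in several places, and the descriptions differ.

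- **Discussion:** "The primary outcomes, centered around effectiveness and safety, encompass the regression of cysts, alterations in menstrual patterns, treatment duration, side effects, and complications". That is five families. The abstract, under Expected outcomes, gives the same five.
- **Primary outcome measures:** six items stand under this heading. Two are effectiveness items (cyst regression, menstrual pattern) and four are safety items (treatment duration, side effects, liver function tests, critical complications).
- **Statistical analysis:** effectiveness and safety are both treated as belonging to the primary outcomes. The error rate is set once for everything: "The significance level for hypothesis testing will be set at 0.05, and all tests will be two-tailed". No outcome leads, and no order is given.
- **Introduction:** "The primary objective is to evaluate the efficacy of these interventions in terms of cyst regression and their influence on the menstrual pattern". Safety follows there as an additional focus.

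On blinding, the Allocation section says: "Due to the nature of the interventions, participants cannot be blinded". Outcome assessors and data analysts are to be blinded. For the menstrual outcome, "Participants will record information regarding the frequency, regularity, duration, and volume of their menstrual cycles".

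**The concern.** A primary outcome is the result on which the trial's conclusion rests, and its error rate is the one the trial promises to control. Here almost everything measured carries that label at the same undivided 0.05. A significant difference in any family could be reported as a primary finding, whatever cyst regression shows, and the nominal 5% would not describe the risk of a wrong primary conclusion.

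Bias adds to chance. Menstrual diaries and symptom reports come from women who know which treatment they take, yet they have the same standing as ultrasound read by blinded assessors.

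The sections also disagree on whether safety is primary at all. An analysis plan written from this protocol could not tell which list governs.

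**Working it through.** **Inputs, all from the protocol article**

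- Families called primary: 5 in the abstract and Discussion; 6 in Primary outcome measures, which adds liver function tests.
- Named components: cyst regression 1, menstrual features 4, treatment duration 1, side effects 4, liver enzymes 2, complications 3. Total 1 + 4 + 1 + 4 + 2 + 3 = 15.
- Level: 0.05 two-sided for all tests.

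The article states no overall error rate across its primary outcomes, so there is no figure of its own to reproduce.

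**Step 1: independent tests.** If nothing truly differs, the chance of at least one p < 0.05 among k tests is 1 − (1 − 0.05)^k.

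- k = 2 (the Introduction's narrower objective, one test each): 1 − 0.95² = 0.0975
- k = 5: 1 − 0.95⁵ = 0.226
- k = 6: 1 − 0.95⁶ = 0.265 (0.2649 before rounding)
- k = 15: 1 − 0.95¹⁵ = 0.537

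**Step 2: correlated tests.** The article gives no correlations, so these are assumed. Simulating 200,000 sets of equally correlated normal test statistics gives:

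| Assumed pairwise correlation | 5 families | 6 families | 15 components |
|---|---|---|---|
| 0.3 | 21% | 24% | 46% |
| 0.5 | 18% | 21% | 36% |
| 0.8 | 13% | 14% | 20% |

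**Step 3: rare events in the 15-component case.** A discrete test on a rare event does not use its full 5%. With 46 per arm, two-sided Fisher's test gives p = 0.056 for 5 versus 0 events and p = 0.026 for 6 versus 0, so thromboembolism can hardly contribute. Taking 42 per arm, independent components and assumed event rates (1% for thromboembolism and drug interactions, 10% for delayed cycles), the total is:

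- about 40% with Fisher's test for the side effects and complications, side effects at 10%;
- about 50% with Chi-square, side effects at 20%.

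**Step 4: does the sample size reveal the deciding outcome?** No. The Sample size section uses a mean-difference formula with δ = 0.3 (reduced to 0.09), SD 1 and an undivided 5% level, and it attaches these to no named outcome. Cyst regression is to be compared by Chi-square or Fisher's exact test, which does not match a mean difference. The arithmetic of that section is a separate matter.

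**Step 5: what keeping every family primary would take.** Bonferroni levels would be 0.05/5 = 0.0100 or 0.05/6 = 0.0083. At 90% power, the sample size ratio to a single test at 0.05 is ((z + 1.28)/(1.96 + 1.28))². With z = 2.58 and 2.64 this gives about 1.4 and 1.5.

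**The case against.** The strongest defence has five parts.

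1. **Number of tests.** A reader might infer that all 15 components are tested separately, so that a false positive is more likely than not. The article does not say so. It treats the incidence of side effects as one item, and it introduces the symptoms and complications as examples: "Adverse events, including nausea, vomiting, weight gain, and acne, will be documented and assessed for severity and causality". Independence is also implausible. Treatment duration follows cyst response ("We will determine the duration of treatment necessary for each participant by monitoring their response and progress during follow-up appointments"), delayed cycles overlap with menstrual frequency and regularity, and ALT and AST come from the same blood tests. This part stands. The family-level figures are the ones to use.
2. **Blinding.** A reader might infer that only ultrasound is protected. The Allocation section blinds outcome assessors without limiting this to ultrasound, and liver enzymes are laboratory values. This stands too. The open-label concern applies to diaries and self-reported symptoms.
3. **Decision rule.** The article does not say that any single significant outcome suffices to declare a treatment better. A multiplicity rule is commonly left to an analysis plan, which is not shown, so its absence is not the finding. Menstrual change is also first assigned paired, within-group tests, so counting that family as a between-arm test rests on the general comparison that follows.
4. **Liver tests.** The abstract's list is worded as non-exhaustive and the Discussion is a summary, so this mismatch is minor.
5. **Endpoint definition.** The article speaks of regression. It mentions cysts dissipating only as the point where ultrasound follow-up ends. Complete disappearance is therefore not a definition the documents fix.

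None of this answers the core point. The article actively labels both effectiveness and safety as primary, and this conflicts with its own primary objective. An analysis plan can add a multiplicity rule, but choosing the primary outcome is the protocol's job.

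**Conclusion.** The point holds at the level of outcome families. Five or six families are called primary at a common two-sided 0.05, no outcome leads, and the Introduction's primary objective is narrower.

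The chance of at least one false-positive primary result is 23% to 26% under independence and about 13% to 24% with assumed correlations of 0.8 to 0.3. This assumes one between-arm test per family at full 5% size and no true difference. Even the Introduction's two families would give just under 10% if independent.

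The 54% figure needs 15 separate, independent, full-size tests. The article does not state that design, and rare events make it implausible, so calling a false positive likely is not supported. What is supported is that the 5% rate does not hold for the primary conclusion and that no single result has been designated to carry it.

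**What to change.** Name one primary outcome: cyst regression by three months on assessor-blinded ultrasound, compared between arms at two-sided 0.05. The Chi-square or Fisher comparison already in Statistical analysis can serve. The investigators should state in advance the binary definition of regression. The false-positive risk on the primary question is then 5%.

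Make menstrual pattern and treatment duration secondary. Report side effects, liver tests and complications as safety outcomes, with estimates and 95% confidence intervals. Bring the abstract, Introduction, Primary outcome measures, Statistical analysis and Discussion into line with this.

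The cost is redrafting. Study status says the trial has not started, so the choice can still be made before any outcome is seen. The registry record was not available; if it carries the same list, it needs the same change. The downside is that menstrual and safety results can no longer be called primary. Keeping every family primary with a Bonferroni split would instead need about 1.4 to 1.5 times the sample size of a single test at 0.05, at 90% power.
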